### 2.4. Data Management

Behavioural testing is conducted on HP laptops with 15.6” screens, set up identically for each field psychologist. The laptops are encrypted using BitLocker and synchronised with a secure OneDrive cloud folder at the Jagiellonian University that collects raw data from every test performed. 

To minimise the impact of the study on the environment and to reduce transcription from paper to computer, the psychological data are—wherever possible—collected digitally using online questionnaires implemented in survey tools developed by Qualtrics (https://www.qualtrics.com, accessed on 23 December 2021). 

The raw data are processed and prepared for import in R and Python. To allow easy data selection and extraction of variables of interest by data analysts, a secure user website will be implemented that will interface with an SQLite database.

### 2.5. Study-Specific Questionnaires

Two questionnaires have been developed for the study: a General Questionnaire, and an Address Questionnaire. The General Questionnaire is a Qualtrics-based tool filled in by a legal guardian that collects data on confounders, effect modifiers, and additional exposures. Some items were adopted from the existing studies [37,38,39,40], and some of the items were invented for the purpose of NeuroSmog. Briefly, information on socio-demographics, pregnancy and early life, general health, habits, academic performance, home, and neighbourhood environments of the child is being collected (see Supplementary File S1 for a paper-adopted version of the questionnaire). Non-response options are always presented as a variation of “not applicable”, “don’t know”, “don’t wish to respond”, and at the same time, all responses are forced. The General Questionnaire was validated on a small sample of volunteers. 

The Address Questionnaire collects full prenatal and postnatal residential history of the study participants, as well as preschool and school addresses, hours spent in preschools and at schools, and the transportation mode used (see Supplementary File S2). It is a pencil-and-paper questionnaire. The collected addresses are being geocoded and will be used to assign air pollution estimates, as well as other geographical exposures.

### 2.6. Psychological Evaluation

Cognitive functioning is examined using the Stanford-Binet Intelligence Scales, 5th edition (SB5, [41] and tests from the Diagnostic Battery for Cognitive Functions Evaluation PU1, [42]). These tests measure attention, working memory, and executive function, which represent domains relevant to both classroom learning and ADHD [43]. Guardians complete the Polish adaptations of the Third Edition of Conners’ Rating Scales [44] and Child Behaviour Checklist (CBCL) for Ages 6–18 [45], providing information on ADHD and other externalising and internalising behavioural issues. Children complete the Polish adaptation of Youth Self-Report (YSR) [46], which is a child-completed version of the CBCL [45,47].

Social functioning is assessed using two questionnaires. The first is the Polish adaptation of the Family Adaptation and Cohesion Evaluation Scales (FACES-IV) questionnaire (Skala Oceny Rodziny; SOR) [48], which measures family function, communication, and family satisfaction. The SOR is completed by both guardians and children. The second is the Polish Siblings Relationship Questionnaire (Kwestionariusz Relacji z Rodzeństwem W Okresie Adolescencji; KRR) [49], which is completed only by children with siblings. 

### 2.7. Behavioural Tasks

The attention network task (ANT) measures the efficiency of the three attentional networks—orienting, alerting, and executive functioning [50]. The ANT demonstrates high immediate test–retest reliability, and scores are not correlated across individuals, suggesting that each network efficiency can be measured somewhat independently [51]. We use the children’s version of the ANT, with timing and task stimuli operationalised identically to those used in [50] with the exception that, since our subjects are older, cue duration is set to 100 ms (as in the adult version). 

The continuous performance test (CPT) is a variant of the Go/NoGo task which allows quantification of deficits in attentiveness, impulsivity, activation/arousal, and vigilance. The CPT has high three-months test–retested reliability [52] and has been validated in children with ADHD and in healthy controls [53]. During the task, geometric figures appear (250 ms) on the computer screen in 18 consecutive blocks of 20 trials (360 trials total). The geometric figures are identical to those used subsequently in the functional MRI (fMRI) variant of the Go/NoGo task. The interstimulus interval (ISI) is set to either 1, 2, or 4 s during each block. Participants are asked to press the spacebar in response to each letter presentation, except for the square and the circle [54]. The proportions of Go to NoGo trials are set at 80% and 20%, respectively [55]. 

All children complete practice runs of both tests until their performance reaches 90% accuracy.

### 2.8. Neuroimaging

All neuroimaging data are acquired at the Małopolska Centre of Biotechnology, Jagiellonian University in Kraków, Poland, on a Siemens MAGNETOM Skyra 3T MRI scanner (Erlangen, Germany) using a 64-channel head coil. Participants are familiarised with the scanner and trained to remain still using a mock scanner (https://pstnet.com/, accessed on 23 December 2021). The mock scanning session lasts for 10 min. During the scan, head movements are constrained by inflatable Pearltec pillows (www.pearl-technology.ch, accessed on 23 December 2021). 

The protocol includes T1-weighted (T1-w), T2-weighted (T2-w), and magnetization-prepared 2 rapid acquisition gradient echo (MP2RAGE) structural images, diffusion-weighted imaging (DWI), two resting-state fMRI (rsfMRI), and two task fMRI runs (see Table 2 for detailed acquisition parameters and order). The scanning protocol, including instructions, lasts for one hour. 

The acquisition sequences for T1-w, T2-w, and fMRI neuroimaging data were adopted from the Adolescent Brain Child Development (ABCD) project [56].

The DWI acquisition sequence was adapted from the UK Biobank (www.ukbiobank.ac.uk, accessed on 23 December 2021) to fit the study scanner and includes multiple b-value volume acquisitions. For the fMRI and DWI acquisitions, we use multi-band accelerated echo planar imaging (EPI) pulse sequences developed by the Center for Magnetic Resonance Research at the University of Minnesota [57,58].

The T1-w sequence provides a better contrast-to-noise ratio in white matter and is used for cortical and subcortical segmentation of the brain [59]. The T2-w sequence allows for the discrimination of structural differences in cerebral fluid-filled regions. The combined use of T1-w/T2-w allows the generation of ratio-based cortical myelin maps [60]. It also provides the anatomical reference for rsMRI and task fMRI data, including anterior–posterior commissure alignment. For improved quality, the T1-w and T2-w protocols include volumetric navigators for prospective motion correction [61]. MP2RAGE achieves a spatially uniform contrast [62] and is used for morphometric analyses of brain anatomy and for construction of cortical myelin maps. DWI enables visualisation and characterisation of white matter tracts [63]. rsfMRI imaging allows for the inference of the intrinsic organization of large-scale brain networks [64]. 

Throughout the structural, MP2RAGE, and DWI acquisitions, participants watch neutral-valence movies (e.g., nature documentaries on the life of birds); throughout the rsfMRI acquisition, participants are instructed to stay awake, to keep still, and to blink normally while looking at a fixation cross.

Finally, task fMRI analyses can target task-dependent whole-brain activity and functional connectivity [65,66]. Based on our hypotheses, we chose an fMRI task that measures response inhibition as a measure of executive functioning, as inhibitory control is positively associated with cognitive flexibility and problem-solving skills and, thus, represents an important functional domain during brain maturation [67]. In addition, diminished inhibitory control is associated with disorders of impulse control, including ADHD [68,69]. This task is identical to the conditioned approach response inhibition task (CARIT) used in the Human Connectome Project–Development (HCP–D) project [70] and is a variant of the Go/NoGo task. The task allows mapping of differential neuronal activity when response inhibition demands are high (NoGo trials) as compared to free prepotent motor execution (Go trials) [52]. The task uses a rapid event-related fMRI design with jittered inter-trial intervals (1000–4500 mm) and randomized inter-target intervals to optimize statistical efficiency [71]. During each run, participants view shape stimuli (*n* = 92) and are instructed to press a button as quickly as possible in response to every shape (Go; *n* = 68) except for a circle and a square (NoGo; *n* = 24) [70,72]. 

Region-of-interest measures will be exported from appropriate MRI analysis packages, including FreeSurfer (http://surfer.nmr.mgh.harvard.edu/; accessed on 23 December 2021), Statistical Parametric Mapping (SPM) 2 (www.fil.ion.ucl.ac.uk/spm, accessed on 23 December 2021), and the Oxford Centre for Functional MRI of the Brain Software Library (FSL; https://fsl.fmrib.ox.ac.uk, accessed on 23 December 2021), and analysed in R [36] using logistic regression, with common best statistical practices such as applying corrections for multiple comparisons. Whole-brain measures will be calculated within the MRI analysis packages themselves and statistical tests appropriate to each imaging modality will be applied. For example, for task fMRI data, we will apply a voxel-wise threshold of either *p* < 0.01 or *p* < 0.001 and an appropriate cluster-level threshold (*p* < 0.05, false discovery rate, FDR).

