Emissions of many air pollutants in the European Union (EU) have decreased over the past three decades, and air quality is gradually improving. In particular, between the years 2000 and 2014, significantly decreasing trends in annual average concentrations of PM with an aerodynamic diameter <10 µm (PM_10_) and nitrogen dioxide (NO_2_) were reported [27,28]. Despite these improvements, EU urban populations are exposed to PM levels that exceed the WHO limits for the protection of human health [29]. Between 2000 and 2010, the daily limit value for PM_2.5_ and PM_10_ concentrations in the EU were exceeded from 16 to 52% and from 18 to 44% of days, respectively [29]. These exceedances of PM limit values have mostly been observed in the eastern EU countries of Bulgaria, the Czech Republic, Slovakia, and Poland [28,29]. 

Most of the PM pollution in Poland results from the combustion of coal and other fossil fuels in power and heat generation, and from traffic emissions [30,31]. Estimates of the mortality attributable to PM_2.5_, based on air quality monitoring data for Poland, have demonstrated that the urban Polish population experiences an unduly high impact from particulate air pollution on their health [32]. Annual deaths attributable to air pollution in Poland were estimated at 39,800 for the year 2000, increasing to 47,300 deaths for the year 2017 [33]. 

The overall objective of the NeuroSmog study is to assess whether long-term exposure to outdoor PM affects brain function, structure, and connectivity in both healthy children and in those diagnosed with ADHD. Primarily, we will focus on the effect of PM on neural systems for attention and inhibitory control. In addition to neuroimaging, impacts of PM on these systems will be investigated using behavioural tests, including IQ. To meet the study aim, we assembled a multidisciplinary team of experts comprising air pollution modellers, environmental epidemiologists, neuroscientists, and clinical psychologists.

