**Neuroimaging**	
T1-w and T2-w	Volume of subcortical structures
	Cortical grey matter thickness and surface
DWI	Fractional Anisotropy in regions of interest (tractography)
	NODDI
Task fMRI	BOLD activation in the NoGo > Go contrast in the CARIT
	Amplitude of BOLD signal change between task-related and default-mode-network activations
Resting-state connectivity	Functional connectivity in regions of interest
T1-w, T2-w, and MP2RAGE	Cortical myelin content

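### Section 2.8 names logistic regression for region-of-interest brain measures that are continuous outcomes of PM exposure; the model type needs correcting and aligning with Section 2.10

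*Protocol article*

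**What the plan says.** Section 2.8 (Neuroimaging) states: "Region-of-interest measures will be exported from appropriate MRI analysis packages", and that they will then be "analysed in R [36] using logistic regression". No other model is named for these measures. The same paragraph treats whole-brain measures separately, with tests suited to each imaging modality.

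The Introduction fixes the direction of the question. The overall objective is to "assess whether long-term exposure to outdoor PM affects brain function, structure, and connectivity in both healthy children and in those diagnosed with ADHD", and it adds: "Primarily, we will focus on the effect of PM on neural systems for attention and inhibitory control".

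Table 4 lists the imaging outcomes. They include "Volume of subcortical structures", "Cortical grey matter thickness and surface", fractional anisotropy and functional connectivity in regions of interest, the NoGo versus Go BOLD contrast, and cortical myelin content. The table gives no cut-points. Its only clearly binary main outcome is ADHD diagnosis.

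Section 2.10 (Planned Analyses) names PM2.5, PM10 and NO2 in several windows as exposures, lists brain measures among the outcome domains, and says that each exposure–outcome pair will be analysed by regression. It does not say which kind.

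**The concern.** Logistic regression needs a binary dependent variable, and the ROI measures are not binary. An analyst following Section 2.8 literally would have to cut each brain measure into two classes or turn the model round so that case status is the outcome and the brain measure a predictor. The first loses information and replaces a mean difference per unit of PM with an odds ratio at an arbitrary cut. The second answers a different question, and a case–control design makes it look natural. If neither is intended, the model for these outcomes is in effect undecided, and it could be chosen after the data are seen.

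**Working it through.** The article gives no alpha, power or effect size behind its sample size, so there is no planned power figure to reproduce. The intended numbers in Section 2.2 agree with each other: 267 cases + 533 controls = 800, and 533/267 = 2.00.

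**Inputs.** n = 800 (Section 2.2). Assumed, because the article gives none: two-sided alpha of 5%, a normally distributed ROI measure, independent children, and standardised PM effects of 0.05 to 0.15. Each simulated setting used 1,000 replicates.

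**Reading 1: fit the model directly.** Logistic software refused a simulated cortical thickness as outcome, because the dependent variable must lie between 0 and 1.

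**Reading 2: dichotomise at the median.** For a small effect on a normal outcome, efficiency relative to the linear model is φ(0)² / (½ × ½) = (1/2π) / (1/4) = 2/π = 0.637. The information in 800 children then equals that in 0.637 × 800 ≈ 509. Simulated power:

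| Assumed standardised effect | Linear model, continuous ROI | Logistic model, median split |
|---|---|---|
| 0.05 | 28.8% | 20.0% |
| 0.08 | 60.7% | 44.0% |
| 0.10 | 79.1% | 61.1% |
| 0.12 | 93.3% | 77.6% |
| 0.15 | 99.2% | 92.1% |

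As a check, √0.637 = 0.798, so a median split at 0.10 should behave like a linear analysis at about 0.08. The table gives 61.1% and 60.7%.

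**Reading 3: ADHD as outcome, ROI as predictor.** Data were simulated with a real PM effect on the ROI measure (0.15) and no link between ROI and ADHD. In a logistic model of ADHD on ROI and PM, the ROI coefficient was significant in 5.1% of runs, which is the nominal rate. The coefficient reflects the brain–ADHD association and does not register the PM–brain effect.

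**The passages side by side.** Section 2.8 is specific about the model but names neither the dependent variable nor the exposure. Section 2.10 is specific about outcome and exposure but not about the model. Taken together they assign a binary-outcome model to continuous outcomes.

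**The case against.** The strongest reply is that Section 2.10 governs the analysis. It pairs pollutants with brain outcomes and promises regression of an unspecified kind, which includes linear regression. The wording in Section 2.8 may then be a slip for linear regression in a condensed article whose full plan is not shown. Much of this stands: the sections can be reconciled by a small edit. It does not remove the error, because Section 2.10 neither names linear regression nor overrides the one model that Section 2.8 does name.

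A reader might infer that the planned analysis cannot estimate the PM–brain association at all, so that the primary objective is lost. The documents do not support that. Section 2.10 leaves linear models open, and whole-brain analyses, including task fMRI, have their own tests. Even a dichotomised measure would give an estimate, though a weaker one on another scale.

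A reader might also take the power loss as a consequence of the plan. It is not, because no dichotomisation is described. Nor does the article say which Table 4 outcomes pass through the ROI export. Only fractional anisotropy and functional connectivity carry that label; including subcortical volume and cortical thickness is a reasonable inference.

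**Conclusion.** The concern holds in limited form. The model named for ROI measures in Section 2.8 does not fit continuous outcomes of PM exposure, and it must be reconciled with Section 2.10. That conclusion rests on the text alone and needs no assumed effect size.

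The figures show what one literal reading would cost: about 36% of the information with a median split, and 7 to 18 percentage points of power at assumed effects of 0.05, 0.10 and 0.15 (29 to 20, 79 to 61, 99 to 92). They depend on the assumptions listed and ignore clustering by town, which would lower power under either model if outcomes are correlated within towns. Whole-brain analyses and the ADHD diagnosis outcome are outside the point.

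**What to change.** In Section 2.8, replace the logistic model with linear or linear mixed regression, with the continuous ROI measure as dependent variable and PM as exposure. Say the same in Section 2.10, naming the model type by outcome scale. The statement should also cover three things:

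- **Case–control sampling.** Cases are oversampled (267 to 533), so a pooled model that ignores case status can be biased. Use a case-status term with a PM interaction, analyses stratified by case status, or sampling weights. The first two also deliver the separate effects in healthy children and children with ADHD that the objective asks for.
- **Clustering.** Allow for correlation within town, for example with a random intercept. School is a sampling unit for controls only (Section 2.2), so it should not be treated as one for cases.
- **ADHD diagnosis.** Reserve logistic regression for this outcome. Do not condition on town, since that would remove the between-town PM contrast for which the towns were chosen (Section 2.1).

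The cost is a sentence or two in each section. No new data, measurements or participants are needed.

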### 2.9. Air Pollution Exposure Assessment

Three health-relevant air pollutants are considered for this study: PM_2.5_, PM_10_, and NO_2_. Annual and monthly grids of air pollutant concentrations will be created for the study area for the period from 2007 to 2022 using hybrid land use regression (LUR) models, following methods developed by de Hoogh and colleagues [73,74]. Interestingly, the research evaluating the performance of various regression models, regularization techniques, and machine learning methods for air pollution spatial modelling has shown relatively small differences in the prediction of accuracy in air concentration between various algorithms [75].

The LUR models are estimated and validated using measurements from the air quality stations for each of the air pollutants and for each year separately, and will also include monthly LUR models for the prenatal period. Routine measurements of these air pollutants are made by Polish Chief Inspectorate of Environmental Protection via a network of air quality monitoring stations [76]. The locations of the monitoring stations (*n* = 179) in the study area are illustrated in Figure 1. Measured air pollution concentrations between 2007 and 2019 are depicted in Figure 4.

Predictor variables for the LUR models are summarized in Table 3, and detailed in Supplementary Table S1. We calculate atmospheric dispersion of air pollutants according to meteorological conditions using the methodology described in [77,78], providing 1-h concentrations of pollutants. We use satellite images to inform about land use changes. Data processing is completed with QGIS geographic information system (GIS) software [79]. 

Land cover predictor variables are calculated for seven girds at the following resolutions: ~4 km × 4 km, 2 km × 2 km, 1 km × 1 km, 500 m × 500 m, 250 m × 250 m, 125 m × 125 m, and 62.5 m × 62.5 m. 

Exploratory and correlation analyses of average air pollutant concentrations from the monitoring stations and the predictor variables are performed to assess temporal and spatial distribution patterns. Optimal resolution for each type of variable applied in the LUR air quality modelling is determined based on physical interpretability and supported with statistical analyses, including machine learning. Predictor variables are included in the LUR model only if they adhere to the predefined direction of effect.

Models are validated with out-of-sample and cross-validations methods using data from the monitoring stations. Model assumptions are checked through the analysis of residuals, as well as visual inspection of quantile–quantile plots. Log transformations are tested to minimize the effect of non-normal errors, and *p*-values are calculated assuming normal distributions of errors. Kriging of air pollution concentrations will be performed, as it is expected to significantly improve model performance of linear regression algorithms for spatial data [75]. All LUR modelling is conducted in R statistical software [36].

Finally, estimates resulting from the LUR models will be assigned to all residential and preschool/school addresses of each study participant. Prenatal, early postnatal, concurrent, and life-long air pollution estimates will be calculated.

### 2.10. Planned Analyses

The main outcomes resulting from psychological evaluation, behavioural testing, and neuroimaging are listed in Table 4.

We are planning to publish several papers using prenatal, early life, and lifetime PM_2.5_, PM_10_, and NO_2_ as exposures. The papers will be grouped by outcome domain:Structural brain measuresFractional anisotropyBrain measures of inhibitory and attentional functions assessed with task fMRIResting state connectivityMeasures of attention assessed by behavioural tasksADHD and other externalizing behavioursIQ

Regression analyses will be used to analyse each exposure–outcome pair separately. We will individually assess associations with every pollutant at every exposure window. We will also consider adjusting our models for residuals of co-pollutants, given that PM and NO_2_ tend to be strongly correlated. Confounder sets will be selected using directed acyclic graphs (DAGs) [80] to avoid overadjustment. 

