### 2.2. Study Design and Study Population

Recruitment of study participants began in October 2020, with the aim of having 800 children complete all study procedures by the end of 2022. We are recruiting one ADHD case (intended number *n* = 267) per two population controls (intended number *n* = 533).

Cases with ADHD diagnosis according to the 11th revision of the International Classification of Diseases and Related Health Problems (ICD-11) [35] are recruited by field psychologists in the study towns. Children at risk of ADHD are referred to the psychologists either by cooperative school psychologists or teachers, or by paediatricians, psychologists, psychiatrists, or neurologists from psychological-educational counselling centres and mental health centres. In addition, cases are also recruited from families who voluntarily contacted us after seeing our recruitment advertisements.

We use a two-step model to verify and eliminate ADHD diagnosis in cases and controls, respectively (see Section 2.6). Firstly, a comprehensive psychological assessment is administered and evaluated by field psychologists. Secondly, three consultant clinical psychologists review the assessments to verify the diagnoses according to the ICD-11. Cases that do not meet the ICD-11 criteria are excluded from the study; controls who meet the ADHD diagnostic criteria are recruited into the case arm. 

All study participants are fluent Polish speakers, aged between 10 and 13 years, have average or above average intelligence (i.e., attend non-specialised schools), are in grades IV–VI, and attend school in the selected towns. Exclusion criteria for all are diagnosed intellectual disability, neurological or comorbid psychiatric disorders, other serious medical conditions, as well as contraindications to MRI. Children born before the 35th week or after the 40th week of gestation, or with birth weight <2500 g or with an Apgar score <8 are also excluded. As we are interested in the long-term effects of air pollution, children who resided outside of Poland during the last year are also excluded, as are children whose legal guardians are not fluent in Polish. 

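### The optional adjustment for co-pollutant residuals, read plainly, would leave essentially all confounding by NO2 in the PM coefficient

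*Protocol article*

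**What the plan says.** Section 2.9 of the protocol article states that "Three health-relevant air pollutants are considered for this study": PM2.5, PM10 and NO2. Section 2.10 sets the base analysis as one exposure and one outcome at a time: "Regression analyses will be used to analyse each exposure–outcome pair separately", and "We will individually assess associations with every pollutant at every exposure window". It then adds: "We will also consider adjusting our models for residuals of co-pollutants", and gives the usually strong correlation between PM and NO2 as the reason. The next sentence reads: "Confounder sets will be selected using directed acyclic graphs (DAGs) [80] to avoid overadjustment".

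The article does not say which pollutant is regressed on which, whether the chosen confounders also enter that regression, or which coefficient will be read as the co-pollutant-adjusted effect. It names no other co-pollutant method. The only regression type it names is for region-of-interest imaging measures, which are to be "analysed in R [36] using logistic regression, with common best statistical practices such as applying corrections for multiple comparisons". Most main outcomes in Table 4 are continuous (volumes, thickness, reaction times, IQ, behaviour scores). ADHD diagnosis is binary.

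**The concern.** NO2 can confound the PM estimate only through the variation it shares with PM. Residualising NO2 on PM removes exactly that shared part, so the covariate that remains has nothing with which to correct the PM coefficient. PM keeps the whole of the shared component, whichever pollutant caused it. The higher the correlation, the larger that component. The article gives the strong correlation as its reason for using residuals, yet this is the setting in which the device does least for the PM estimate.

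The stated objective concerns PM specifically, with NO2 as a co-measured exposure. Several papers by outcome domain are planned, so a PM coefficient that looks adjusted but is not could recur across them.

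**Working it through.** The article gives no power, effect-size or correlation figure on this point, so there is no stated number to reproduce.

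**Inputs**
- n = 800, the target in section 2.2 ("with the aim of having 800 children complete all study procedures by the end of 2022"; 267 + 533 = 800).
- PM–NO2 correlation r: not given. Assumed 0.7, 0.8 and 0.9.
- True PM effect 0, NO2 effect 0.20 SD, error variance 1, standardised pollutants: all assumed.

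**Algebra (linear model).** Let e = NO2 − fitted(NO2 | PM, C), where C is the covariate set. Then e is orthogonal to PM and to C. By the Frisch–Waugh–Lovell result, the PM coefficient in Y ~ PM + C + e equals that in Y ~ PM + C. The coefficient of e is the two-pollutant NO2 coefficient.

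**Expected PM coefficient without covariates.** Both the single-pollutant and the residual-adjusted model give 0 + 0.20 × r:
- 0.20 × 0.7 = 0.14
- 0.20 × 0.8 = 0.16
- 0.20 × 0.9 = 0.18

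**How often it is significant.** SE ≈ 1/√800 = 0.0354. The chance of significance is about Φ(coefficient/SE − 1.96):
- r = 0.7: 0.14/0.0354 = 3.95, Φ(1.99) ≈ 97.7%
- r = 0.8: 0.16/0.0354 = 4.52, Φ(2.56) ≈ 99.5%
- r = 0.9: 0.18/0.0354 = 5.08, Φ(3.12) ≈ 99.9%

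**Both pollutants as measured.** The expected PM coefficient is 0. VIF = 1/(1 − r²), and the SE is multiplied by √VIF.

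| r | VIF | SE multiplier | SE of PM |
|---|---|---|---|
| 0.7 | 1/0.51 = 1.96 | 1.40 | 0.050 |
| 0.8 | 1/0.36 = 2.78 | 1.67 | 0.059 |
| 0.9 | 1/0.19 = 5.26 | 2.29 | 0.081 |

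**Simulation (4,000 runs per correlation).** Residual-adjusted PM coefficients averaged 0.141, 0.160 and 0.180. They differed from the single-pollutant coefficients by less than 1e-14 and were significant in 97.7%, 99.5% and 99.9% of runs. With both pollutants entered, the mean was about 0 and false positives were 4.6–5.4%.

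**Where exact equality fails.** A second simulation included one measured confounder, true PM effect 0, NO2 effect 0.3 (linear) or 0.6 log-odds (logistic), n = 400,000 and correlation 0.73. PM coefficients were:

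| Model | PM alone | + NO2 residual, same covariate in both steps | + NO2 residual, covariate omitted from residual step | + NO2 as measured |
|---|---|---|---|---|
| Linear | 0.209 | 0.209 | 0.244 | −0.001 |
| Logistic | 0.403 | 0.418 | 0.490 | −0.003 |

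Equality is exact in one residual cell only. In the other three the coefficient moves, but away from the true value of 0. One town random-intercept example gave 0.261 alone, 0.239 with the residual and 0.026 with NO2 itself. Those fits raised convergence warnings and are indicative only.

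**The case against.** The strongest reply is that the article does not fix the method. The adjustment is only under consideration, the residual is undefined, and a condensed article may leave such detail to an analysis plan that is not shown. Every pollutant is to be analysed in turn, so an NO2 model could carry a PM residual, and the coefficient of that residual is exactly the two-pollutant PM effect. Using PM residualised on NO2 as the exposure, with NO2 in the model, recovers the same quantity. The confounder selection step also does not exclude a co-pollutant as a covariate.

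The algebra in this reply is right, and it shows that a residual form can be used properly. But it requires interpreting the residual's own coefficient, or residualising the exposure. The text instead describes adjusting a model for the co-pollutant's residual. Optional status limits how firmly the point can be put, but does not make the method work if it is used.

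Three stronger readings are tempting and should be resisted.
- A reader might infer that the PM coefficient is unchanged in every model. That is exact only for linear models with matched covariates; logistic regression is named in section 2.8 and ADHD diagnosis is binary.
- A reader might infer near-certain false positives in this study. The 98% or more depends on assumed effects and correlations, and on the unfavourable case of no PM effect at all.
- A reader might infer that the authors will present PM results as robust to co-pollutants. The article nowhere says this, nor that the residual model removes NO2 confounding.

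**Conclusion.** The point holds in limited form. Under the plain reading, the only co-pollutant method the article names does not control the PM effect for NO2. The PM coefficient keeps essentially all of the shared component in the linear and logistic variants checked. With no true PM effect and an NO2 effect of 0.20 SD, that means a spurious PM coefficient of about 0.14 to 0.18 over correlations of 0.7 to 0.9. The algebra is certain; the size rests on assumed correlations and effects, since the article supplies neither. The conclusion also rests on NO2 being regressed on PM and on the PM coefficient being the one interpreted. The wording should be changed before the analyses are run.

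**What to change.** Replace the sentence in section 2.10 with a two-pollutant model that enters PM and NO2 as measured, reported beside the single-pollutant model with its variance inflation factor. An equivalent form in linear models uses PM residualised on NO2 and the model's covariates as the exposure, with NO2 and those covariates in the model.

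If residuals are kept, state which pollutant is regressed on which, with which covariates, and which coefficient is interpreted. Do not describe the PM coefficient from a model containing PM plus an NO2 residual as adjusted for NO2.

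The change is to wording and reporting only; no new data are needed. The price is precision: PM intervals about 1.4, 1.7 and 2.3 times wider at correlations of 0.7, 0.8 and 0.9. That loss reflects how little the data can separate the two pollutants, and the variance inflation factor lets readers see it.
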